## Materials and methods

Trial design

The study will employ a two-arm, parallel, single-blinded cluster randomized trial by using multistage sampling to evaluate the effectiveness of X-SIAGA in enhancing household outbreak preparedness against Disease X and outbreaks among the Orang Asli in Selangor. In this two-sided superiority trial design, the intervention group will receive the X-SIAGA intervention and educational brochures, while the control group receives only the brochures. The protocol adheres to the Standard Protocol Items: Recommendations for Interventional Trials (SPIRIT) guideline [22]. The SPIRIT schedule of enrollment, allocation, and assessments is shown in Table 1. 

**Table 1 TAB1:** SPIRIT's schedule of enrolment, interventions, and assessments for X-SIAGA intervention. SPIRIT: Standard Protocol Items: Recommendations for Interventional Trials [22].

	Studt Period					
	Enrolment	Allocation	Post-allocation			
Timepoint	0	0	Baseline Assessment (T_0_)	Immediately Post-intervention (T_1_)	One-Month Post-intervention (T_2_)	Three-Month Post-intervention (T_3_)
Enrollment:						
Eligibility screen	X					
Informed consent		X				
Allocation		X				
Intervention:						
X-SIAGA intervention				X		
Standard educational brochure (control)				X		
Assessments:						
1^st^ questionnaire administration			X			
2^nd^ questionnaire administration				X		
3^rd^ questionnaire administration					X	
4^th^ (final) questionnaire administration						X

Theoretical and conceptual frameworks

This study applied the Social Cognitive Theory (SCT) and the Health Belief Model (HBM) to guide the development and implementation of the X-SIAGA intervention, aiming to influence the Orang Asli’s cognition, health beliefs, and behaviors related to household preparedness for Disease X and outbreaks. SCT is a widely used theory in disaster and emergency health preparedness programs, alongside the HBM. While the HBM focuses mainly on individual beliefs, SCT considers a wider array of factors, highlighting the interaction between behavioral, cognitive, and environmental influences in predicting behavior. Perceived self-efficacy, a cognitive aspect in SCT and part of individual health belief in the HBM, shapes how individuals view their environment and affects their intentions and actions [23].

In this study, Cognitive Preparedness refers to the mental process of preparedness, specifically the knowledge, attitudes, and health beliefs a person holds regarding readiness for Disease X and outbreaks. Preparedness Behavior refers to the observable actions or practices carried out in preparation for such events. Literature suggests that effective preparedness requires both cognitive and behavioral components. Individuals need to have sufficient knowledge and positive attitudes and health beliefs, and they must also demonstrate these through actual preparedness behaviors [12,13]. Therefore, *Household Outbreak Preparedness* is defined as a continuum that integrates both *Cognitive Preparedness* and *Preparedness Behavior* to best reflect the overall level of preparedness [24]. The theoretical framework is presented in Figure 1, and the conceptual framework is presented in Figure 2.

**Figure 1 FIG1:**
[figure not shown]
Theoretical framework.

**Figure 2 FIG2:**
[figure not shown]
Conceptual framework. Hypothesis 1 (H1): The intervention changes household preparedness levels, potentially improving their capability to respond to Disease X and potential outbreaks; Hypothesis 2 (H2): The intervention changes cognitive aspects related to preparedness, improving knowledge and attitudes, including health beliefs, towards Disease X and outbreaks; Hypothesis 3 (H3): The intervention changes behavioural aspects related to preparedness, enhancing skills and tangible preparedness practices among households for Disease X and outbreak preparedness.

Study setting and participants

The trial will take place in Orang Asli settlements in Selangor that are gazetted and listed under the Department of Orang Asli Development (JAKOA), focusing on the Orang Asli community members as the study population.

Recruitment

For each selected district, a JAKOA representative is engaged to support the study. The JAKOA representative contacts the village leader of eligible villages to gauge interest in participating. If the village leader expresses interest, an initial meeting is scheduled on a mutually agreed date involving JAKOA, the village leader and committee members, and the research team. During this meeting, the study is explained in detail, and any questions or concerns are addressed. Once the village leader and committee members express their commitment, they are provided with a study information sheet, eligibility criteria, participant expectations, and an ethical information statement.

The study is then promoted by the village leader and committee members to eligible participants. A list of interested and eligible individuals is shared with the research team. The research team prepares a WhatsApp invitation, which is sent to and forwarded by the village leader to the listed participants. Participants who attend the baseline assessment on the agreed date and time are briefed on the study and the consent process. Those who provide written informed consent will complete a baseline assessment and follow their cluster’s assigned intervention. Data collection will commence after participants have signed the informed consent forms.

Sample size

Using the formula for a two-arm parallel-group design in cluster trials [25], the trial requires a minimum sample size of 30 households for each arm. The calculations are as follows:

\begin{document} m = \frac{(Z_{1-\alpha/2} + Z_{1-\beta})^2 \, 2\sigma^2}{\Delta^2} \left[ 1 + (n - 1)\rho \right] \end{document}

where *m* is the number of households per arm; *Z_1−α/2_* is the standard error associated with a 95% confidence interval (*Z_1−α/2_*=1.96); *Z_1−β_* is the standard error associated with 80% power (*Z_1−β_*=0.842); Δ is the mean awareness score difference between the pre- and post-assessments in the intervention group within a community-based trial on disaster preparedness intervention (Δ=15.97) [26]; σ^2^ is the total variation in awareness score between the pre- and post-assessments in the intervention group within the same trial (σ^2^=138.949) [26]; *n* is the estimated median number of households in Proto-Malay majority Orang Asli villages in Selangor (*n*=54) [18]; and ρ is the intracluster correlation coefficient (ICC) (ρ=0.048) [27].

Allowing for an anticipated attrition rate of approximately 30%, the ideal sample size was set at 45 households per arm. Following the CONSORT Statement recommendation that each study arm should include at least four clusters [28], this study employs multistage sampling to select four Orang Asli villages per arm, aiming for 12 households in each village, a total of 96 households for the study.

Eligibility criteria

Table 2 outlines the eligibility criteria for clusters at both the district and village levels. Meanwhile, Table 3 provides the inclusion and exclusion criteria for participants who will represent their households by participating in X-SIAGA and completing a questionnaire designed to assess the change in preparedness scores at all data collection points.

**Table 2 TAB2:** Eligibility criteria for district and village level clusters.

District	Village
Districts in the state of Selangor.	Villages that have not previously participated in any outbreak preparedness programs.
Districts with gazetted Orang Asli villages.	Villages with more than 12 households.
Districts with more than 5 Orang Asli villages.	Villages accessible via road transport.

**Table 3 TAB3:** Inclusion and exclusion criteria of participants.

Inclusion criteria	Exclusion criteria
Orang Asli descent.	Having physical or cognitive disabilities (e.g., blindness, deafness, schizophrenia and dementia).
Malaysian citizen.	Having severe health conditions (e.g., respiratory and cardiovascular disease requiring oxygen support such as severe asthma, Chronic Obstructive Pulmonary Disease, heart failure and congenital heart diseases).
Age 18 years old and above.	Residing temporarily (less than 2 years).
The head of the household, or the person who contributes to, or influences health-related decisions for the household.	Intending to relocate to a different village within the next 2 years.
Live in a household with more than two members.	
Able to converse, read and write in Malay.	

Sampling, randomization, allocation, and blinding

The study utilizes a multistage sampling approach with computer-generated randomization for the allocation of villages into the intervention or control arm. Due to potential variability in participant numbers and logistical challenges, simple randomization is employed over block randomization for its flexibility and straightforward, unbiased allocation. The entire sampling, randomization, and allocation process is conducted independently by an external health professional with research experience.

First, two districts in Selangor are randomly selected from the eligible pool. Within each district, four villages are randomly chosen. These villages are then divided, with two randomly allocated to the intervention group and two to the control group in each district (i.e., each district has two intervention villages and two control villages). This approach aims to achieve homogeneous sociodemographic groups among the households. Household recruitment in each village is voluntary, facilitated by JAKOA, village leaders, and committees, targeting 12 households per village.

Given the nature of the intervention, the authors are inevitably aware of group allocation. Procedures are identical for both groups, and research assistants are not provided with information about the study sequence or allocation; hence, they remain uninformed about group assignment. Participants in both groups will remain blinded to their allocation throughout the study.

Intervention

The X-SIAGA intervention package was developed by using the Intervention Mapping framework, and its development process will be reported in a separate publication. Table 4 provides a concise overview of the components and activities included in the X-SIAGA intervention. In the intervention group, households from four Orang Asli villages will receive educational brochures on communicable disease prevention and participate in the X-SIAGA intervention during a one-day program in their respective villages. Two eligible adults from each household will participate in the intervention activities.

**Table 4 TAB4:** Summary of the components and contents of X-SIAGA intervention package.

Component	Contents
Lecture	Introduction to Disease X and outbreak.
	Importance of Household Outbreak Preparedness.
Video presentation	Video presentation on previous outbreaks and discussion.
Experience sharing	Sharing personal experiences with past outbreaks and discussion.
Practical session	Pre-Outbreak: (i) Infection prevention practice: Practicing the 7-step hand hygiene; (ii) Preparedness planning: Developing a household preparedness plan for outbreaks and Disease X.
	During and post-outbreak: (i) Suspecting an outbreak: Recognizing potential symptoms of Disease X and signs of outbreak through a puzzle game; (ii) Outbreak response: Learning what to do in the event of an outbreak through a sequencing game; (iii) Life-saving skills for emergency situations: Performing Hands-Only Cardiopulmonary Resuscitation (CPR).
Simulation exercise	Role-playing three different possible real-life situations: (i) Pre-Outbreak scenario; (ii) During outbreak scenario; (iii) Hands-only CPR scenario.
Game-based learning	“Wabak X” card game play session.

The intervention will be delivered by the authors, assisted by a team of research assistants who are independent of any institutions associated with the authors. All research assistants received prior training and were actively involved at an early stage, including during the pilot phase of the trial.

Each household will also receive a booklet that includes the materials covered during the X-SIAGA program. Participants start using the booklet during the program, and they take it home for self-study with other family members and to complete their household outbreak preparedness plans. Additionally, they will receive a set of the “Wabak X” card game and are encouraged to play it with their family members. The pair of adults representing their household will complete a questionnaire to assess the change in preparedness scores at all data collection points.

This study aims to assess the effectiveness of X-SIAGA under realistic conditions. This means there will be no refresher sessions or reminders. Instead, only follow-ups at specific time points for data collection will occur. This approach is designed to mirror real-world conditions, as health promotion programs conducted by various local agencies, including government ministries and community organizations, are typically held only once or at most twice per year.

Control

In the control group, households from four Orang Asli villages receive only educational brochures on communicable disease prevention, without the X-SIAGA intervention package. These brochures, sourced from the District Health Office, are currently used by the public health promotion team for education on awareness and prevention of infectious diseases and outbreaks in local communities. Similarly, two eligible adults from each control group household will participate in the research activities and complete the questionnaire at all data collection points. The control group will receive the X-SIAGA intervention package after data collection for all participants is completed.

Data collection

Data collection will be conducted by using the Household Outbreak Preparedness Evaluation (HOPE) questionnaire, administered at four intervals: (i) before the intervention (T0); (ii) immediately after the intervention, with the intervention group having received both the X-SIAGA intervention and educational brochures and the control group having received educational brochures only (T1); (iii) at one month post-intervention (T2); and (iv) at three months post-intervention (T3). The HOPE questionnaire is an adapted and translated instrument based on prior studies on household preparedness for outbreaks and general disasters [15,24]. Validation of the HOPE questionnaire will be published elsewhere. The questionnaire is self-administered, with assistance available from trained research assistants and representatives of the village committee if participants require support.

Outcome measures

The scoring for the HOPE questionnaire follows Sumaja’s methods [24]. The primary outcome measure, the Household Outbreak Preparedness score, represents the equally weighted average of the Cognitive Preparedness and Preparedness Behavior scores. By using Sumaja’s preparedness matrix [24], scores will be normalized to a scale of zero to one, and a cut-off value of 0.5 at the x- and y-axes will categorize households’ outbreak preparedness into four groups: Fully Prepared, Committed, Aware, and Unprepared.

Secondary outcome measures include the Cognitive Preparedness and Preparedness Behavior scores. The Cognitive Preparedness score assesses household knowledge, attitudes, and health beliefs, while the Preparedness Behavior score evaluates the skills acquired and practices adopted by households to prepare for potential Disease X and outbreaks.

Control of bias

To prevent contamination bias, the study ensures sufficient geographical separation between intervention and control villages to minimize interactions among participants from different groups. Prior to recruitment, the research team held meetings with village leaders and committee members, in the presence of JAKOA officials, to explain the X-SIAGA intervention, emphasize the importance of strict confidentiality, and discourage discussions about the intervention. These leaders and committee members then conveyed this information to eligible participants during household recruitment. All participants will again receive a detailed explanation of the privacy and confidentiality policy when expressing interest in joining the trial, and only those who provide consent will be enrolled. To mitigate attrition bias, the study will employ an Intention-to-Treat (ITT) approach. Additionally, to sustain motivation and engagement, perishable goods will be offered as incentives at each stage of data collection.

Statistical methods

The statistical analysis for this study will be carried out by using the IBM SPSS Statistics for Windows, Version 26 (Released 2018; IBM Corp., Armonk, New York). Descriptive statistics will include frequency and percentages for categorical data and mean and standard deviation for numerical data.

To compare baseline sociodemographic characteristics between the intervention and control groups, a Pearson Chi-Square test will be utilized for categorical variables, while an Independent Samples t-test will be used for continuous variables. To evaluate changes over time from T0 to T3 between and within the groups, a repeated-measures analysis of variance will be conducted. To assess variation in results between and within the groups across the different time points, while also controlling for potential confounding variables, a generalized estimating equation will be utilized.

Statistical analyses will use a two-tailed test to evaluate the superiority hypothesis. The null hypothesis states that there is no difference between the X-SIAGA intervention package and standard educational brochures. A significance level of 0.05 will be applied.

Data management

To manage missing data and outliers, corrective actions will be taken to recover or validate entries. The research team will reach out to the participant for clarification and ensure accurate data entry. The Last Observation Carried Forward method will be utilized for uncontactable dropouts. A sensitivity analysis will be performed to determine how using the ITT approach with imputed data might affect study conclusions.

During the research, data will be managed carefully to ensure privacy and confidentiality. All data generated will be de-identified and anonymous, with the principal investigator being the only one with access to identifiable information. Results will be presented in aggregated form to prevent reidentification of any individual or address. The findings from this study will be disseminated as conference abstracts, posters, and presentations, and manuscripts will be developed for publication from the study findings.

Individual participant data will be shared only upon reasonable request and will require approval from UiTM and the Ministry of Health Malaysia (MOH). These datasets will not contain any identifiers. Participants may request access to their own results and to the general study findings, but not to other participants’ data.

All data will be stored in soft-copy format on a password-protected computer and archived on a secure, password-protected flash drive to prevent data loss or damage. Data will be retained for seven years after publication, after which it will be securely destroyed by deleting and overwriting the files.

Trial registration, ethics approval, and consent to participate

This study has been registered at ClinicalTrials.gov (NCT06539845) and has received ethical approval from the National Medical Research Registry/Medical Research and Ethics Committee (Ref: 24-01859-NQ7) and the Universiti Teknologi MARA Research Ethics Committee (Ref: REC/10/2024 (PG/FB/33)).

This study adheres to the Malaysian Code of Responsible Conduct in Research to ensure data confidentiality and compliance with ethical standards. Engagement with the indigenous community throughout the study is conducted in a manner that is mutually beneficial, respectful, and sensitive to cultural norms. Participants are provided with a study information sheet that offers detailed information about the study’s purpose, procedures, and what participation entails. This information is given during recruitment advertisements and again before participants give consent.

Consent will be secured through written consent forms from participants before joining the study. Informed consent will be obtained by the research team, with assistance from representatives of village committee members provided as needed to ensure full understanding of the information. Investigators are available to answer any questions, and ample time is given for consideration of involvement in the study. All prospective participants are informed that participation is entirely voluntary. Withdrawal from the study is permitted at any time without any negative consequences, and there is no requirement to disclose reasons for withdrawal.

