The generalizability of the findings might be limited due to the unique aspects of the Orang Asli community in Malaysia. The Orang Asli community in Selangor may also not be representative of Orang Asli tribes from other states, as some can be very different from one another. Furthermore, nonrandom household recruitment could lead to homogeneous views within social networks, and individuals holding village roles or being more vocal might disproportionately influence the study’s findings.

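### Villages are allocated before household consent and baseline, and no stated safeguard keeps the arm from those who recruit households, so recruitment could differ between arms

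*Protocol article*

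**What the plan says.** The section on sampling, randomization, allocation and blinding samples two districts, then four villages in each, and then allocates: "These villages are then divided, with two randomly allocated to the intervention group and two to the control group in each district". Only after this does it turn to households: "Household recruitment in each village is voluntary, facilitated by JAKOA, village leaders, and committees, targeting 12 households per village". An external health professional carries out sampling, randomization and allocation. The same section accepts that "the authors are inevitably aware of group allocation".

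The Recruitment section gives the route to households. "The study is then promoted by the village leader and committee members to eligible participants". Next, "A list of interested and eligible individuals is shared with the research team", and the village leader forwards the invitation to those listed. On the baseline day, "Those who provide written informed consent will complete a baseline assessment and follow their cluster’s assigned intervention".

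The section on control of bias adds that "Prior to recruitment, the research team held meetings with village leaders and committee members, in the presence of JAKOA officials, to explain the X-SIAGA intervention". It also says that leaders and committee members passed this information on to eligible people while recruiting.

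Table 1 marks the eligibility screen under enrolment, consent and allocation together in the allocation column, and the first questionnaire (T0) under post-allocation. Enrolment and allocation share time point 0.

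**The concern.** Randomizing villages makes the villages comparable in expectation. It makes the enrolled households comparable only if they are identified before the arm is known, or by people who do not know it. Here consent and T0 come at or after allocation, recruitment is voluntary, and it passes through local people whom the research team has briefed on X-SIAGA.

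The arms offer different things. One gives two adults per household a one-day programme, a booklet and a card game. The other gives brochures, with X-SIAGA after data collection ends. The Discussion itself expects hopes of immediate personal benefit to affect recruitment and retention. If the arm is known while households are being approached, different households may come forward in the two arms.

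Such a difference would enter the comparison of Household Outbreak Preparedness scores directly, in a direction that cannot be predicted. Baseline comparisons and the planned generalized estimating equation with confounders can deal with measured differences. They cannot deal with unmeasured motivation.

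**Working it through.** **Step 1: order of events.** Three places in the article bear on it.

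| Place | What it shows |
|---|---|
| Sampling and randomization section | Villages allocated 2:2 per district, household recruitment described afterwards |
| Table 1 | Eligibility screen before allocation, consent in the allocation column, T0 post-allocation |
| Recruitment section | Those who consent follow an arm already assigned to their village |

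All three agree that the arm is fixed by the time of consent and T0. Whether households are first listed before or after allocation is less certain. The order of the text points to after; the eligibility screen in Table 1 leaves room for before.

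**Step 2: what each stated safeguard covers.**

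| Safeguard | Protects | Covers leaders, committees, JAKOA? |
|---|---|---|
| External randomizer | Sequence and draw | No |
| Research assistants not told the allocation | Assistance at sessions | No |
| Participants blinded | Participants' knowledge of arm | Not as recruiters |
| Identical procedures in both groups | Uniform conduct | Indirectly; nothing on who knows the arm when |

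No step closes the household list before the arm is released, and none draws households at random.

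**Step 3: the plan's own figures.** From the sample size section: Z values 1.96 and 0.842, Δ = 15.97, σ² = 138.949, n = 54, ρ = 0.048.

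- (1.96 + 0.842)² × 2 × 138.949 / 15.97² = 8.555
- 1 + 53 × 0.048 = 3.544
- 8.555 × 3.544 = 30.3, against 30 stated
- 31 / 0.7 = 44.3, rounded up to 45 as stated; 2 × 4 × 12 = 96 as stated

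These figures reproduce, and the point does not depend on them.

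**Step 4: how much a shift would matter (illustration).** With 48 households per arm, 12 per village and no attrition:

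- design effect 1 + 11 × 0.048 = 1.528
- standard error √(2/48 × 1.528) = 0.252 SD
- detectable with 80% power, t on 8 − 2 = 6 degrees of freedom: (2.447 + 0.906) × 0.252 = 0.85 SD; with normal quantiles, 2.802 × 0.252 = 0.71 SD
- planned effect: 15.97 / √138.949 = 1.35 SD

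An assumed shift of 0.2 to 0.3 SD between arms is then 24% to 35% of 0.85 SD, 28% to 42% of 0.71 SD, or 15% to 22% of 1.35 SD.

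**Step 5: false-positive rate under one-sided selection (illustration).** Twelve of a median 54 households is 22%. The mean of the top 22% of a standard normal variable is 1.34 SD. Suppose willingness to be listed correlates r with the outcome and acts in one arm only. The bias is then b = 1.34r SD, and the two-sided error at a nominal 5% is Φ(b/0.252 − 1.96) + Φ(−b/0.252 − 1.96).

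| r | Bias (SD) | Two-sided error |
|---|---|---|
| 0 | 0 | 5% |
| 0.1 | 0.13 | 8% |
| 0.2 | 0.27 | 19% |
| 0.3 | 0.40 | 36% |

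If the same selection acts in both arms, the bias cancels. The documents give no value for r or for the shift.

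**The case against.** A reader might infer that leaders know their village's arm, hand-pick 12 households accordingly, and are briefed by the unblinded authors in person. The article supports none of this outright. It nowhere says that leaders are told their arm. It describes promotion, volunteering and a list of interested, eligible people with no stated length; 12 is a target. It says that the research team held the meetings, and that this includes the authors is a reasonable inference only.

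Several features also lessen the risk. The briefing is not described as differing by arm, procedures are called identical, participants are stated to be blinded, and control villages are to receive X-SIAGA later, so leaders in either arm may expect it. Selection that is alike in both arms limits generalizability without biasing the comparison. The Discussion concedes that much in saying that "nonrandom household recruitment could lead to homogeneous views within social networks". Finally, a condensed article may leave the moment at which the allocation is released to the full protocol.

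These objections remove any claim that biased recruitment is established. They do not remove the point. The order of allocation, consent and T0 is stated, not left out, and it is the order that opens the route. No stated safeguard covers the people who recruit. The limitation in the Discussion concerns shared views and vocal individuals, not selection that differs between arms.

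**Conclusion.** The point holds as a risk built into the stated sequence. Allocation precedes consent and T0, the authors know it, and nothing in the article keeps it from the leaders, committees and JAKOA staff through whom households are recruited. Differential recruitment is therefore possible. Whether it occurs, in which direction and by how much cannot be told from the documents.

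The figures of 0.2 to 0.3 SD and error rates of 8% to 36% rest on assumed shifts and on selection acting in one arm only. They show that modest selection would matter; they are not estimates. The error rates also use normal quantiles, and a reference distribution suited to eight villages would give somewhat smaller inflation. The planned adjustment is useful but limited to what is measured, so the remedy belongs in the design.

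**What to change.** - The external health professional who already performs the randomization should keep the allocation from authors, leaders, committees and JAKOA. It should be released only when all selected villages in a district have submitted final household lists and, preferably, completed consent and T0.
- Use one neutral script at all village meetings.
- Where more than 12 eligible households volunteer, have the 12 drawn at random.
- Move allocation after baseline in Table 1.
- If the arm is already withheld in this way, one sentence saying so and a corrected Table 1 are enough.
- Where recruitment has begun (the village meetings are reported in the past tense), document who knew each village's arm and when, and report numbers listed, invited and consenting by arm.

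The cost is a short amendment and a re-ordering of steps, with no extra staff and no change in sample size. The drawback is that the programme day cannot be scheduled by arm until lists close, and it may need a separate date from T0.
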